## **Background**

Pancreatic surgery is associated with a significant risk for postoperative complications, particularly for pancreatic anastomotic insufficiency, which lead to pancreatic fistula and other complications. Various methods have been examined in order to reduce this complication. Recently a large randomized controlled trial was published from the United States, which showed that pasireotide is effective in reducing postoperative pancreatic fistula (Allen et al., 2014). Based on this trial, our institution began the use of pasireotide in preventing postoperative pancreatic fistula in high risk patients, whose pancreas is soft and/or pancreatic duct narrow. Last year a Finnish research group published a similar study, which showed that perioperative cortisone treatment reduces complications and postoperative fistulas similarly as pasireotide in the aforementioned trial (Laaninen et al., 2014,2015). In both trials, the experimental drug was compared to placebo, and no study comparing these two drugs to one another has been carried out. Since pasireotide is more expensive than cortisone, it is important to find out whether the efficacy in preventing complications is at the same level, and cortisone could replace pasireotide as the standard preventive drug.

## **Hypothesis**

Cortisone is non-inferior to pasireotide in preventing postoperative pancreatic fistula and complications

## **Methods**

### **Sites**

Abdominal Center, Helsinki University Hospital

### **Intervention groups**

- 1) Perioperative pasireotide treatment  
Patient receives 900 microg of pasireotide s.c. twice a day starting at the morning of the day of surgery, and continues until the 6th postoperative days evening dose (total 14 doses)
- 2) Perioperative cortisone treatment  
Patient receives 100mg of hydrocortisone i.v. three times a day starting at the morning of the day of surgery, and continues until the 2th postoperative days evening dose (total 9 doses)

Apart from the drug give according to the intervention group (pasireotide or cortisone), the treatment of patient is according to the normal routine after pancreatic resection.

### **Study patients**

**Inclusion criteria**

- Patient scheduled for pancreatic resection (pancreaticoduodenectomy, distal resection, enucleation, or other resection)

**Exclusion criteria**

- Atrophic pancreas or markedly dilated pancreatic duct visible at computed tomography at the site where pancreaticojejunostomy will be reconstruction (applies only to patients scheduled for pancreaticoduodenectomy)
- Patient is scheduled for total pancreatectomy
- Allergy or other contraindication for cortisone or pasireotide
- Age < 18 y
- No written informed consent

**Criteria to remove patients from analyses after randomization:**

- Pancreatic resection was not performed (e.g. disseminated cancer)
  - Hard pancreas and/or dilated pancreatic duct (so called low risk pancreas) (applies only to patients undergoing pancreaticoduodenectomy – the decision is made intraoperatively)
  - Patient withdraws consent (data collected until withdrawal will be used in the study)
- NOTE! Unmasking or premature stopping of the trial drug will not remove patient from the trial.

**Randomization**

Patients will be randomized 1:1 to receive either perioperative pasireotide or cortisone treatment. Randomization will be done computer assisted using randomly variable block size. All patients, who fulfill inclusion criteria and do not meet exclusion criteria, will be randomized and allocated treatment will be commenced before surgery. A piece of paper indicating the allocated group will be put in an opaque envelope (so called safety envelope). The envelopes will be numbered and they are opened in numerical order.

**Blinding**

Because one drug is given s.c. and the other i.v., patients and nurses cannot be blinded. The study will be commenced so called single-blinded, in which the treating doctors and researchers are unaware of the allocation group. The envelope in which the allocation group is concealed will be opened by a study nurse, who marks this in Miranda (EHR) as “pancreatic fistula study drug” instead of the drug’s real name. The real name of the drug is marked on a separate place, so that the treating doctors will not see which drug the patient will receive inadvertently. The administration of drugs will be scheduled so that they will occur only after the treating doctors rounds, so that the blinding will not be unmasked. In case the treating doctors need to know which drug was administered (e.g. significant adverse event suspicion, change in treatment, etc), the blinding will be unmasked, and the treating doctor may find out which drug the patient has received. Any unblinding will always be marked in Miranda (EHR) either in orders section or in normal health record text on Surgery page.

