## **Schedule**

The study will be commenced directly after receiving the permissions to conduct it, estimated at spring 2016. Approximately 100 pancreatic resections are being performed in Helsinki University Hospital annually, and approximately 50 – 60 of these are estimated to be suitable for the trial. Recruiting period is estimated to take approximately 2 years, after which primary and secondary outcome measures can be analyzed and published. Tertiary outcomes will be analyzed when 1, 5, or 10 years have passed from the recruitment of the last patient. Interrim analysis will be made when half of the patients have been recruiting, meaning at 62 patients. Complication outcomes will be analyzed, and based on these the decision whether it is safe to continue study will be made.

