## **References**

Laaninen M, Sand J, Vasama K, Laukkarinen J. Whipplen leikkauksen jälkeisiä komplikaatioita voidaan vähentää hydrokortisonihoidolla. *Randomoitu*

plasebokontrolloitu tutkimus. Suomen Kirurgiyhdistys ry 2015 36;4

Collected parameters

Name

Social security number

Date of birth

Gender (1 = male, 2 = female)

Charlson comorbidity index

Medication

Anticoagulation (0 = no, 1 = yes)

Immunosuppression (0 = no, 1 = yes)

Cortisone (0 = no, 1 = yes)

Date of diagnosis of pancreatic tumor (suspicion) (=computed tomography date)

Preoperative diagnosis (1 = pancreatic cancer, 2 = cholangiocarcinoma, 3 = IPMN, 4 = NET, etc)

Neoadjuvant therapy (0 = no, 1 = gemcitabine, 2 = folfirinox, 4 = chemoradiotherapy, 4 = other)

Randomization group (1 = signifor, 2 = cortisone)

Date of surgery

Type of surgery (1 = whipple, 2 = distal resection, 3 = enucleation, 4 = median pancreatectomy, 4 = exploration, 5 = total pancreatectomy, 6 = other)

Venous resection (0 = no, 1 = portal/SMV, tangential or end-to-end, 2 = porta/SMV,

Arterial resection (0 = no, 1 = yes)

Pancreaticojejunostomytype (1 = Heidelberg, 2 = [name], 3 = other)

Consistency of pancreas (1 = hard, 2 = soft, normal)

Pancreatic duct at operation (1 = small, normal, 2 = dilated)

Pancreatic duct size, computed tomography, mm

Drains (0 = no, 1 = one drain, 2 = two drains)

Was study drug continued after operation (1 = yes, 2 = no, hard pancreas/dilated duct in patient undergoing whipple, 3 = no, no operation, 4 = no, total pancreatectomy)

Complications, 30 days from operation

Pancreatic fistula, ISGPS grade

DGE, ISGPS grade

Postop haemorrhagia, ISGPS grade

First complication, C-D class

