First complication, description (1 = pancreatic fistula, 2 = DGE, 3 = postop haemorrhagia, 4 = pulmonary embolism, 5 = pneumonia, 6 = UTI, 7 = superficial wound infection, 8 = deep wound infection, etcetc)

Second complication, C-D class

Second complication, description (1 = pancreatic fistula, 2 = DGE, 3 = postop haemorrhagia, 4 = pulmonary embolism, 5 = pneumonia, 6 = UTI, 7 = superficial wound infection, 8 = deep wound infection, etcetc)

Third complication, C-D class

Third complication, description (1 = pancreatic fistula, 2 = DGE, 3 = postop haemorrhagia, 4 = pulmonary embolism, 5 = pneumonia, 6 = UTI, 7 = superficial wound infection, 8 = deep wound infection, etcetc)

Fourth complication, C-D class

Fourth complication, description (1 = pancreatic fistula, 2 = DGE, 3 = postop haemorrhagia, 4 = pulmonary embolism, 5 = pneumonia, 6 = UTI, 7 = superficial wound infection, 8 = deep wound infection, etcetc)

Fifth complication, C-D class

Fifth complication, description (1 = pancreatic fistula, 2 = DGE, 3 = postop haemorrhagia, 4 = pulmonary embolism, 5 = pneumonia, 6 = UTI, 7 = superficial wound infection, 8 = deep wound infection, etcetc)

Sixth complication, C-D class

Sixth complication, description (1 = pancreatic fistula, 2 = DGE, 3 = postop haemorrhagia, 4 = pulmonary embolism, 5 = pneumonia, 6 = UTI, 7 = superficial wound infection, 8 = deep wound infection, etcetc)

Postoperative amylase level at day 3

Postoperative drain amylase level at day 3

Postoperative blood sugar level, highest during hospital stay

Date of commencement of normal per oral feeding

Date of discharge

Destination of discharge (1 = home, 2 = primary care ward, 3 = referring hospital)

Referring hospital's name (1 = Helsinki University Hospital, 2 = Lappeenranta, 3 = Lahti, 4 = Kotka, etc)

PAD

Histology (1 = pancreatic ductal adenocarcinoma, 2 = cholangiocarcinoma, 3 = IPMN, 4 = NET, etc)

pT category

pN category

pM category  
Number of examined lymph nodes  
Number of metastatic lymph nodes  
R category

Re-admission, 30 days (0 = ei, 1 = yes)

Reason, free text

Was the blinding unmasked to treating doctors (0 = ei, 1 = yes, inadvertently, 2 = yes, advertently unmasked)

Reason, free text

Date of study drug stopping

Adverse event of study drug (0 = no adverse events, 1 = nausea, 2 = elevated blood sugar, etc)

Postoperative outpatient clinic visit (0 = no, 1 = yes, Helsinki University Hospital)

Adjuvant therapy (0 = no, 1 = gemcitabine, 2 = folfirinox, etcetc)

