## **Sökkoutus**

Koska toinen lääke annetaan s.c. ja toinen i.v., ei potilaita tai hoitohenkilökuntaa voida sökkouttaa. Tutkimus tehdään ns. yksöissökkeutetusti, jolloin hoitavat lääkärit ja tutkijat eivät tiedä kumpaan ryhmään potilas kuuluu. Potilaan ryhmän kertovan kirjekuoren avaa potilasta hoitava hoitaja, joka kirjaa Mirandan lääkelistalle lääkkeen nimeltä "haimafistelitutkimuslääke", ja sen lisätietoihin tarkemmin kumpi lääke on kyseessä. Näin ollen lääkärit eivät tiedä kumpaa lääkettä potilas tulee saamaan. Lääkkeiden annot ajoitetaan niin, että ne tapahtuvat vasta lääkärin kierron jälkeen, jotta annettava lääke ei paljastu lääkäreille. Mikäli hoitavilla lääkäreillä on tarve tietää kumpaa lääkettä potilas on saanut (esim. merkittävä haittavaikutusepäily, hoidon muutos, tms), puretaan sökkoutus, ja

lääkäri voi käydä katsomassa kumpaa lääkettä potilas on saanut. Sökkoutuksen purkamisesta/purkautumisesta tehdään aina merkintä Mirandan määräysosioon (ns. nuijan alle) tai sairaskertomustekstiin KIR-lehdelle.

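### The promised blinding of treating doctors and researchers is not secured by the procedures the protocol describes

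*Protocol*

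**What the plan says.** The protocol describes a single-blind trial. It concedes that "Because one drug is given s.c. and the other i.v., patients and nurses cannot be blinded", but states that "treating doctors and researchers are unaware of the allocation group" (Blinding). Four measures support this: a neutral study-drug label in the electronic record, the real name held elsewhere, dosing after the doctors' rounds, and a record of every unblinding.

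Other parts of the protocol bear on whether these measures suffice:

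- **Intervention groups.** Pasireotide is given subcutaneously twice a day and ends with the sixth "postoperative days evening dose (total 14 doses"). Hydrocortisone is given intravenously three times a day and ends with the second "postoperative days evening dose (total 9 doses"). No dummy dosing is described.
- **Finnish text, Sökkoutus.** The nurse enters the neutral name on the medication list "ja sen lisätietoihin tarkemmin kumpi lääke on kyseessä", that is, with the drug's identity in the additional information of that entry. The English text keeps the name in a separate location. The English text has a study nurse open the envelope; the Finnish text has the nurse caring for the patient do so.
- **List of collected parameters (after the References).** One list holds "Randomization group (1 = signifor, 2 = cortisone"), the ISGPS grades, the Clavien-Dindo class of each complication, "Date of study drug stopping" and the adverse events of the study drug. Unmasking is recorded for treating doctors only.

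**The concern.** The primary outcome is the 30-day CCI, which is built from Clavien-Dindo classes (Sample size). Those classes depend partly on what doctors decide to do about a complication and partly on the judgement of whoever grades it. With patients and nurses open, the blinding of doctors and researchers is the main stated protection of the primary comparison.

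If doctors or graders can work out the arm, care or grading may shift with their expectations. In a non-inferiority trial, a shift towards cortisone makes a false non-inferiority claim more likely, and a shift against it costs power. Because the protocol records unmasking only for treating doctors, a grader's knowledge of the arm would leave no trace in the data.

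**Working it through.** **1. What the label cannot hide.** Inputs are from Intervention groups.

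| | Pasireotide | Hydrocortisone |
|---|---|---|
| Doses per day | 2 | 3 |
| Last day | postoperative day 6 | postoperative day 2 |
| Days of treatment | 7 (days 0 to 6) | 3 (days 0 to 2) |
| Total doses | 7 × 2 = 14 | 3 × 3 = 9 |

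The totals agree with the protocol. The courses end 4 days apart. On days 3 to 6 (4 of the 7 pasireotide days, 4 × 2 = 8 of the 14 doses) an entry still active points to pasireotide. An ended entry suggests hydrocortisone, although early stopping is also possible. Frequency differs from the first day. All of this falls within the 30-day CCI window. It reveals the arm only to someone who can see frequency or status, and the protocol does not say that these are hidden.

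**2. Where the name is recorded.** A separate location (English) and the additional information of the same medication entry (Finnish) are different procedures. Under the Finnish one, the allocation lies within the entry that carries the neutral label.

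**3. Who sees what when grading.** The parameter list contains the arm in clear and two further fields that can point to it: the stop date (day 2 against day 6 in a completed course) and study-drug adverse events. The list does not say who grades or that any field is withheld from the grader.

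**4. How much a bias could matter.** The protocol gives no figure for bias, so its size is assumed here.

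The planned sample size comes first: margin 9, SD 20, true difference 0, one-sided 5% (the 90% interval in the Statistical analysis plan section). Power is not stated; 80% reproduces the figure.

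n per group = 2 × 20² × (1.645 + 0.842)² / 9² ≈ 61.1, rounded up to 62, as stated.

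Standard error of the mean difference at 62 per group: 20 × √(2/62) = 3.59.

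Let b be the CCI points by which grading or care favours cortisone. The difference is read as pasireotide minus cortisone, which fits the stated −9 limit.

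- False non-inferiority rate at a true 9-point disadvantage: Φ(−1.645 + b/3.59).
- Power at no true difference, with the same bias against cortisone: Φ(9/3.59 − 1.645 − b/3.59).

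| Assumed bias b | False non-inferiority (bias for cortisone) | Power (bias against cortisone) |
|---|---|---|
| 0 | 5.0% | 80.5% |
| 1 | 8.6% | 72.0% |
| 2 | 13.8% | 61.9% |
| 3 | 20.9% | 51.0% |
| 5 | 40.0% | 29.8% |

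The table shows sensitivity only. It does not estimate the bias in this trial.

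**The case against.** The strongest reply is that the masking is real. The protocol has a neutral label, a name kept apart, dosing after rounds and mandatory recording of unblinding. The data include whether treating doctors were unmasked, by accident or on purpose, and why, so leakage to them can partly be measured. That doctors see frequency or active status in the record is assumed. Stopping the drug early does not remove a patient from the trial, so an ended entry on day 3 is not proof of the arm. This stands: it rules out saying that the blind fails, but does not show that it is secured.

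Three stronger readings are tempting, and the document does not support them.

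- **That the data form displays allocation next to the grades.** The document gives a list of variables, with many items between arm and first grade, and no form layout. Any trial dataset must hold both. What can be said is that no separation is stated.
- **That the interim look unblinds the researchers.** The Schedule says "Complication outcomes will be analyzed, and based on these the decision whether it is safe to continue study will be made". It does not say whether results are compared by arm or pooled, or who sees them; an arm comparison is plausible but inferred. Even aggregate results by arm would not reveal any one patient's allocation.
- **That the interim can be judged against p < 0.05.** That level is given for reported superiority p-values and is not tied to the interim. The protocol sets no interim stopping threshold, so error rates computed for one would describe an invented rule.

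**Conclusion.** The point holds in a limited form: the blinding promised for treating doctors and researchers is not secured by the stated procedures. Three facts carry it: courses of different frequency and length behind a label that masks only the name, two contradictory instructions on where the drug's identity is recorded, and no stated separation between allocation-revealing fields and the grading of the primary outcome.

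It rests on two assumptions: that doctors or graders can see dosing frequency, entry status or the listed fields, and that CCI grading leaves room for judgement. The direction and size of any bias are unknown. Against a 9-point margin even a small one would matter: an assumed 2 points takes the false non-inferiority rate from 5% to about 14%, or power from about 81% to 62% in the other direction. The sample size is unaffected. The change should be made, because it is cheap and protects the primary outcome.

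**What to change.** 1. Reconcile the English and Finnish blinding sections on where the drug's identity is recorded and which nurse opens the envelope, so that the identity stays off the entry treating doctors routinely see.
2. Keep allocation, study-drug stop date and study-drug adverse events in a separate file. Withhold it from the researchers who grade CCI, Clavien-Dindo and ISGPS outcomes until those grades are locked. Extend the unmasking item to graders.
3. State in the trial report that the blinding of treating doctors is partial because the courses differ in length.

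The cost is a split data file and slightly more nurse documentation. Doses, schedules and sample size stay as they are. A neutral entry kept open to day 6 in both arms is not proposed, because it would alter a live medication record. A strict interim threshold on CCI alone is not proposed either, because it would lower the chance of detecting harm and narrow the planned safety review.

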**Outcome measures**

Primary outcome

Comprehensive complication index 30 days postoperatively

#### Secondary outcomes

1. Complications (Clavien-Dindo classification), 30 days
2. Rate and severity of postoperative pancreatic fistula (ISGPS classification), 30 days
3. Rate and severity of delayed gastric emptying (ISGPS classification), 30 days
4. Rate and severity of post-pancreatectomy haemorrhage (ISGPS classification), 30 days
5. Length of hospital stay, days
6. Readmissions, 30 days
7. Number of patients received adjuvant therapy among patients with cancer diagnosis

#### Tertiary outcomes

1. Overall survival, 1, 5, 10y
2. Disease-free survival, 1, 5, 10y
3. Disease-specific survival, 1, 5, 10y

Outcome measures will be analyzed in following subgroups: 1) Patients who have undergone pancreaticoduodenectomy, 2) Patients who have undergone distal resection

#### Follow-up

Patients will be followed according to normal postoperative routine, either at Helsinki University Hospital or in referring hospital. If the follow-up will be in referring hospital, patient records from these hospitals will be requested 1, 5 and 10 years from surgery. There is no extra outpatient clinic visits outside normal routine follow-up.

#### Expenses

At the moment, pasireotide is routinely used in patient eligible for the trial in Helsinki University Hospital. Patients will be randomized 1:1 to receive either pasireotide or cortisone. Cortisone is cheaper than pasireotide, so the study will not generate extra expenses, but on the contrary it will save expenses. Hydrocortisone (Solucortef) 100mg injection costs 5.97EUR, so the drug expenses in this arm are total 53,73EUR. Pasireotide (Signifor) 900microg injection costs 73,68EUR, so the drug expenses in this arm are total 1031.52EUR.

#### Collected parameters

See appendix 1.

#### Sample size

Sample size is calculated based on primary outcome, Comprehensive complication index (CCI). CCI is based on Clavien-Dindo (C-D) classification, and CCI takes into account cumulative burden of complications better than C-D classification (Slankamenac et al., 2014). Thus CCI is more sensitive and requires smaller sample size compared to C-D classification. Clinically relevant difference in CCI is set at 10 points. This study will aim to show that cortisone-group does not have more than 9 CCI points more than in the pasireotide-group. Standard deviation (SD) is estimated to be 20 based on earlier publications. Based on sample size calculations 62 patients are required per group to show this, thus total 124 patients.

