## **Statistical analysis plan**

Non-inferiority will be tested by lower limit the mean difference's 90% confidence interval (equivalent of 95% confidence interval of one-sided test). If the lower limit of CCI's mean difference's 90% confidence interval is under -9, non-inferiority is not met. Of primary and secondary outcomes, CCI and length of stay will be presented as mean (standard deviation) and compared between groups using independent t-test with bootstrapping. Only primary outcome will be assessed using non-inferiority testing, and secondary outcomes will be assessed using superiority approach. Categorical secondary outcome measures are compared using Chi square test. Effect sizes are reported either as mean difference with 95% confidence interval or odd ratios (OR) with 95% confidence interval. All p-values reported are two-sided and for superiority testing. P-value <0.05 was considered statistically significant. Missing data, if any, will be reported. Missing data are omitted from analyses of the particular variable in question and no missing data is imputed. All outcomes will be analyzed using modified intention-to-treat analyses, where all randomized patients in whom the study drug is continued after surgery are included in the analyses. Subgroup analyses are performed using superiority testing for patients undergoing pancreaticoduodenectomy or distal pancreatectomy.

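### The 124 patients are counted at recruitment, but the 62 per group must be analysed; planned removals after randomisation have no allowance, so power falls below the implied 80%

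*Protocol*

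**What the plan says.** The Sample size section gives the aim, "This study will aim to show that cortisone-group does not have more than 9 CCI points more than in the pasireotide-group", and the variability, "Standard deviation (SD) is estimated to be 20 based on earlier publications". It concludes: "Based on sample size calculations 62 patients are required per group to show this, thus total 124 patients". The test is set in the Statistical analysis plan section as the "90% confidence interval (equivalent of 95% confidence interval of one-sided test".

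The Schedule section counts the same total at recruitment: "Interrim analysis will be made when half of the patients have been recruiting, meaning at 62 patients". The Finnish version of that section likewise places the interim analysis when 62 patients have been recruited.

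Under Randomization, every eligible patient is randomised and starts the allocated drug before surgery. The criteria for removal from the analyses then include no resection having been done and, for pancreaticoduodenectomy only, an intraoperative finding of "Hard pancreas and/or dilated pancreatic duct (so called low risk pancreas". The Finnish list adds conversion to total pancreatectomy. The English list omits it, but the English appendix codes it as a reason for not continuing the drug. The Statistical analysis plan section defines the modified intention-to-treat set to match: "all randomized patients in whom the study drug is continued after surgery are included in the analyses". Missing values are omitted and not imputed.

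On accrual, of about 100 resections a year, "approximately 50 – 60 of these are estimated to be suitable for the trial", and recruitment is expected to take about two years.

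**The concern.** A sample size formula returns the number of patients who must contribute data to the comparison. The protocol doubles that number to 124 and then uses 124 as the recruitment total, while its own rules take some randomised patients out of the analysis. If any patient is removed and not replaced, fewer than 62 per group remain on average, and the calculation leaves no margin for that.

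In a non-inferiority trial a smaller analysed number widens the confidence interval. The trial could then miss its margin because too few patients were analysed, not because cortisone is worse, and the reader could not tell which. The shortfall makes a failed result more likely; it does not raise the chance of a false claim of non-inferiority.

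**Working it through.** **Inputs.** Margin 9 and SD 20 (Sample size); one-sided 5%, from the 90% interval (Statistical analysis plan); 1:1 allocation (Randomization). Two inputs are not stated and are taken here as 80% power and a true difference of 0.

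**Reproducing 62.** n per group = 2 × (z₀.₉₅ + z₀.₈₀)² × SD² / margin² = 2 × (1.6449 + 0.8416)² × 20² / 9² = 2 × 6.183 × 400 / 81 = 61.06, rounded up to 62. The plan's figure is reproduced exactly. Other combinations do not fit: one-sided 2.5% with margin 9 and 80% power gives 78; one-sided 5% with margin 9 and 90% power gives 85; one-sided 5% with margin 10 and 80% power gives 50. One-sided 2.5% with margin 10 gives 63, which is close but conflicts with the stated margin and interval. This is why 80% is taken as the implied power.

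**Slack.** Power from the noncentral t distribution, with 2n − 2 degrees of freedom and noncentrality 9 / (20 × √(2/n)), is 80.1% at 62 per group and 79.6% at 61. There is no patient to spare.

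**Where the 124 is counted.** The Schedule section equates half of the recruited patients with 62, so the recruited total is 2 × 62 = 124. This equals the number the formula needs in the analysis, so the allowance for removals is zero.

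**Effect of removals.** The protocol gives no removal rate d, so the rates below are assumptions, applied equally to both groups.

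| Assumed removal d | Analysed per group, 62 × (1 − d) | Power (t) | To randomise, 124 / (1 − d) |
|---|---|---|---|
| 0% | 62 | 80.1% | 124 |
| 5% | 58.9 | 78.3% | 131 |
| 10% | 55.8 | 76.3% | 138 |
| 20% | 49.6 | 71.9% | 155 |
| 30% | 43.4 | 66.8% | 178 |

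Numbers to randomise are rounded up; odd totals need one more patient for equal groups.

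**Accrual.** 50 to 60 a year for 2 years gives 100 to 120, against 124. Reaching 124 takes 124/60 = 2.1 to 124/50 = 2.5 years. If the 50 to 60 is counted before removals, which the protocol does not say, 138 randomised takes 2.3 to 2.8 years, 155 takes 2.6 to 3.1 and 178 takes 3.0 to 3.6.

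**The case against.** The strongest reply is that 124 may already mean analysable patients. The Sample size section speaks of patients needed to show the result, the Finnish heading speaks of removing patients from the study, and no sentence caps randomisation at 124. Enrolment could therefore continue until 124 analysable patients are reached. On this view the interim trigger is loose wording about a safety look. This has some force, but both language versions of the Schedule section count recruited patients, and no replacement rule or number to randomise appears. If analysable patients were meant, the protocol needs to say so.

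Several stronger readings are tempting and are not supported:

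- A reader might infer that gland risk is judged only at surgery, so that removals must be frequent. The Exclusion criteria remove atrophic glands and markedly dilated ducts seen on CT, and planned total pancreatectomy, before randomisation. The intraoperative rule catches what remains, and only in pancreaticoduodenectomy. Nothing in the protocol points to 20% or 30%.
- Drug not continued after surgery might be read as a further, separate loss. The appendix codes it only as low-risk gland, no operation or total pancreatectomy, and the note under the removal criteria keeps patients who stop the drug early. Consent withdrawal need not cost a patient either, since data up to withdrawal are used.
- The accrual figures might be read as a contradiction in themselves. Both the rate and the two years are marked as approximate, and the annual figure may already be net of some removals, so they only support the point.
- It might seem that the interim analysis must be counted in modified intention-to-treat patients. It asks whether continuing is safe, and counting all recruited patients is defensible for that purpose.

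**Conclusion.** The point holds. The calculation itself is correct, but its result is attached to the wrong count: 62 per group are needed in the analysis, while 124 is used as the number recruited, and the design removes some of them with no allowance. The direction does not depend on the rate, because any unreplaced removal takes power below the implied 80%.

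The size does depend on it. The loss is about 2 percentage points at 5% removal, 4 at 10%, 8 at 20% and 13 at 30%. These figures rest on the inferred 80% power, a true difference of 0, an SD of 20, equal removal in both groups and rates that the protocol does not give. CT screening may keep the true rate at the lower end.

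**What to change.** In the Sample size section, state the power and the assumed true difference, and say that 62 per group refers to patients in the modified intention-to-treat set. Give the expected removal rate, with its basis, and the resulting number to randomise, 124 / (1 − d). If 124 randomised is a ceiling, restate the size and power at the number expected to be analysed.

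Bring the recruitment count and duration in the Schedule section into line with that choice, and say whether the 50 to 60 a year is before or after removals. Reconcile the English and Finnish removal lists on total pancreatectomy, so that the set to which the 62 refers is the same in both.

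The cost is a few sentences and a less favourable figure: either a lower stated power or a longer stated recruitment period. If the analysable-patient definition is chosen, more patients must be randomised. No new procedure or data item is needed.
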